# A randomized controlled trial investigating the effect of a diet low in fermentable oligosaccharides, disaccharides, monosaccharides, and polyols on the intestinal microbiome and inflammation in patients with ulcerative colitis: study protocol for a randomized controlled trial

**DOI:** 10.1186/s13063-020-4108-7

**Published:** 2020-02-18

**Keywords:** FODMAP diet, Inflammation, Microbiota, RCT, Ulcerative colitis

## Abstract

**Background:**

No conclusive treatment is available for irritable bowel disease (IBD). Adherence to a diet low in fermentable oligosaccharides, disaccharides, monosaccharides, and polyols (FODMAPs) might alleviate clinical symptoms of IBD. However, no study has investigated the effect of low FODMAPs diet on the intestinal microbiota and inflammatory biomarkers in patients with IBD. The aim of current study is to examine the effect a low FODMAP diet on IBD symptoms, inflammation, and the intestinal microbiota in patients with ulcerative colitis.

**Methods and analysis:**

This study is a randomized clinical trial. Thirty patients with mild to moderate ulcerative colitis will be randomly allocated to receive a low FODMAP diet (*n* = 15) or to continue their usual diet as control (*n* = 15), for 4 weeks. The quantity of intestinal microbiota including Clostridium cluster IV, *Faecalibacterium prausnitzii*, Rosburia spp., Lactobacillus spp., Bifidobacteria spp., *Akkermansia muciniphila*, *Bacteroides fragilis*, and Ruminococcus spp., and the *Firmicutes* to *Bacteroidetes* ratio and calprotectin and lactoferrin levels will be explored in fecal samples from patients. In addition, anthropometric measures and biochemical assessments including serum concentrations of highly sensitive-C reactive protein (hs-CRP), tumour necrosis factor-α (TNF-α) and IL-1β will be taken from patients at baseline and end of the study. The study has been registered in IRCT (IRCT20181126041763N1; registration date: 2019-01-18).

**Discussion:**

Consumption of a low-FODMAP diet might decrease systemic and intestinal inflammation, change the bacterial population in the gut, and modulate clinical symptoms in patients with ulcerative colitis. Further studies investigating the effect of such a diet on other variables, including other bacterial species and inflammatory cytokines, are required to confirm future findings of this trial.

## Background

Inflammatory bowel disease (IBD), a chronic gastrointestinal disease with frequent episodes of diarrhea and constipation, usually occurs in adults aged 20–40 years [1]. It imposes a great burden on the health system and personal life [2]. Although not life-threatening, it causes several disabilities, which may continue throughout life [3].

The exact etiology of IBD is still not understood; however, disturbances in the immune system, inflammation, and genetic predisposing factors are among the most identified risk factors [4]. Gut bacteria are suggested to play a role in this regard [5, 6]. Immune dysfunction may damage the natural microflora in the intestine and consequently accelerate IBD symptoms [7]. In addition, changes in the gut microbiota may cause harmful immunological responses in the intestinal mucosa [7, 8].

No conclusive treatment is available for IBD. Restriction of fermentable oligosaccharides, disaccharides, monosaccharides, and polyols (FODMAPs) in some gastrointestinal (GI) problems has been resulted in symptoms alleviation [9, 10]. However, it should be noted that FODMAPs have prebiotic properties in humans [11]. Therefore, a low FODMAP diet might result in reduced growth of beneficial bacteria in the intestine. In addition, fermentation of FODMAPs by the gut microbiota produces a considerable amount of short-chain fatty acids (SCFA), such as butyrate, which could be used as a fuel for intestinal cells [12]. Therefore, although reduction in FODMAPs may alleviate IBD symptoms partially due to reduction in bacterial fermentation [13], the exact mechanism through which a low FODMAPs diet may influence these symptoms are unknown. There is no study available investigating the effect of a low FODMAPs diet on the intestinal microbiota and inflammatory biomarkers in patients with IBD. Therefore, this study aimed to examine the effect of consumption of a low FODMAP diet on IBD symptoms, inflammation and gut microbiota in patients with ulcerative colitis (UC).

## Methods

### Participants

This study is a randomized clinical trial. Participants will be recruited from Shariati and Imam Khomeini hospitals, Tehran, Iran. Subjects (aged 20–60 years, body mass index (BMI) 18.5–30 kg/m^2^) with mild to moderate UC who are in disease remission with stable drug therapy will be selected for this study. UC will be diagnosed by a gastroenterologist using the Mayo score. Scores of 3–8 will be considered as mild to moderate UC [14]. Patients who had changed type or dosage of their medicines over the past month, suffered from other gastrointestinal diseases including cancer and infectious diseases, who are pregnant or breastfeeding, or are using antibiotics, prebiotic or probiotic products, multi-vitamin, and mineral supplements, or tobacco will not be included. We will not include patients who had been hospitalized in the last 3 months or patients with type 2 diabetes mellitus or celiac disease. Individuals who change the type or dosage of their medicines during the intervention, or are hospitalized or develop infection will be excluded. All participants will provide informed written consent. Moreover, the study protocol has been recorded in the irct.ir website (IRCT20181126041763N1; registration date: 2019-01-18). The flow-diagram of the project is shown in Fig. 1. Flow-diagram of study process is shown in Fig 2 (Additional file 1).

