### Study design

The study was designed according to the Standard Protocol Items: Recommendations for Interventional Trials (SPIRIT) 2013 checklist. After recruitment, participants will enter into a 2-week run-in period, during which general information on diet, physical activity, type and dosage of medications will be obtained. All measurements, including anthropometric and biochemical assessments, will be made at this stage, and then participants will be stratified based on age (20–40 and 40–60 years), gender (male/female), body mass index (18.5–24.9 and 25–30), and type of medicines (anti-inflammatory and immunosuppressant) into different strata. Actually, first we will enroll a participant who meets the inclusion criteria in a stratum. Then, based on these variables the second person, who is matched with the first one in that stratum would be gone to the same stratum. So, we would have two similar persons (in terms of the aforementioned variables) in a stratum. Then, the two persons in a single stratum would be randomly assigned into the intervention and non-intervention groups. Therefore, we would have 15 strata (each consisting of two similar persons) in total and then individuals in the strata would be randomly allocated to the aforementioned groups. So, we would have 15 people in each group and the groups would be almost similar in terms of these variables. A person who is not part of the study will randomly allocate participants. Participants in the intervention group will receive a low-FODMAP diet according to their usual dietary intakes, whereas participants in the control group will receive their usual diet without any modification, for 4 weeks. Participants in both groups will receive the usual dietary recommendations for patients with IBD. To evaluate participants’ compliance, three 24-h dietary recalls will be taken throughout the intervention. Participants will be asked not to change their life-style and medicines during the study. Again, all measurements will be examined at the end of trial.

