### Assessment of study outcomes

#### Primary outcomes

The main primary outcomes in the current study would be fecal calprotectin and lactoferrin as well as gut microbiota including Clostridium cluster IV, *Faecalibacterium prausnitzii*, Rosburia spp., Lactobacillus spp., Bifidobacteria spp., *Akkermansia muciniphila*, *Bacteroides fragilis*, and Ruminococcus spp. and the *Firmicutes* to *Bacteroidete*s ratio.

To examine gut microbiota and fecal calprotectin and lactoferrin, stool samples (10 g) from one defecation will be taken from each individual at study baseline and end of trial. The samples will be immediately stored at − 20 C° until further analysis. Bacterial DNA will be extracted using the QIAamp (QIAGEN) commercial fecal DNA kit. Calprotectin is a calcium binding protein commonly derived from neutrophils and monocytes and in to a lesser extent from macrophages [15]. Calprotectin is found in stool and plasma, and its concentration increases throughout inflammatory conditions including IBD, and infection [15, 16]. The quantity of intestinal microbiota including Clostridium cluster IV, *F. prausnitzii*, Rosburia spp., Lactobacillus spp., Bifidobacteria spp., *A. muciniphila*, *B. fragilis*, and Ruminococcus spp., as well as the *Firmicutes* to *Bacteroidetes* ratio, will be determined using commercial real-time PCR kits (QIAamp, QIAGEN). In addition, fecal concentrations of calprotectin and lactoferrim will also be measured using an enzyme-linked immunosorbent assay. Therefore, our primary outcomes will be the mean difference in changes from baseline to 4-week follow up in calprotectin concentrations and quantity of gut microbiota between the intervention and control groups.

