### Study sample size calculation

By considering a type I error of 5% (α = 0.05) and type II error of 20% (β = 0.20, power = 80%) and the primary outcome variable of expected difference between the intervention and control groups in mean fecal calprotectin, calculated based on the two sided *t* test, we calculated the required sample size using the following formula:
$$ n=\frac{{\left({\mathrm{Z}}_{1-\frac{\alpha }{2}}+{\mathrm{Z}}_{1-\beta}\right)}^2\times \left({S_1}^2+{S_2}^2\ \right)}{\left({\upmu_1}^2-{\upmu_2}^2\right)} $$

(S1= 25.88, S2= 21.99, μ1= 26.6, μ2= 4)

Based on this formula and allowing for 10% drop-out in each group, we will need a sample size of 15 persons for each group.

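### Randomised patients who change medicines, are hospitalised or develop infection are excluded, so part of any disease worsening can leave the primary comparison, possibly unequally by arm

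*Protocol article*

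**What the plan says.** The Participants section of the protocol article contains two kinds of rule. The first concerns entry. For example, "Patients who had changed type or dosage of their medicines over the past month" are not taken into the study, and a hospital stay in the preceding three months also bars entry. The second concerns events after the start: "Individuals who change the type or dosage of their medicines during the intervention, or are hospitalized or develop infection will be excluded".

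The Study design section places allocation after the two-week run-in and the baseline measurements, and before the four-week diet: "Then, the two persons in a single stratum would be randomly assigned into the intervention and non-intervention groups". Measurement is at baseline and again at the end of the trial.

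The Primary outcomes section defines what is compared across the arms: "our primary outcomes will be the mean difference in changes from baseline to 4-week follow up in calprotectin concentrations and quantity of gut microbiota". Of calprotectin the same section says that "its concentration increases throughout inflammatory conditions including IBD, and infection".

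The sample size section provides for losses by "allowing for 10% drop-out in each group". The Statistical analysis section names the tests. Nothing in the article says that patients excluded under the second rule are still measured, or are analysed in the group to which they were allocated.

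**The concern.** The events that trigger exclusion happen after randomisation, and two features make them hazardous as grounds for removal.

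- **They are related to the outcome.** Infection is one of the triggers and, by the article's own account, raises calprotectin. A change of medicine or a hospital stay can follow from worsening colitis, which calprotectin also reflects.
- **They can depend on the arm.** The article expects that the diet might lower inflammation and symptoms (Discussion of the abstract), and also that it might reduce beneficial bacteria (Background). Participants given a menu can tell themselves apart from those who keep their usual diet, so decisions to change medicines may also differ by arm.

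If either arm has more such events, the patients who remain are no longer the groups that randomisation made comparable. A diet that prevents such events would lose part of its benefit in the estimate. A diet that provokes them would have part of its harm concealed. Covariate adjustment, which the article plans, cannot be relied on to restore the randomised comparison.

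**Working it through.** **1. Does the rule act on randomised patients?** Yes. Recent medicine changes and recent hospital stays are already covered by the entry criteria. The exclusion sentence speaks of events during the intervention, and Study design puts allocation before the intervention. It cannot be read as an eligibility rule.

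**2. The plan's own figures, for scale.** From Study sample size calculation: means 26.6 and 4, SDs 25.88 and 21.99, two-sided α 0.05, power 80%, 10% drop-out, 15 per group.

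- Planned difference: 26.6 − 4 = 22.6.
- The formula as printed gives (1.960 + 0.842)² × (25.88² + 21.99²) / (26.6² − 4²) = 13.09. Then 13.09 / 0.9 = 14.5, so 15 per group is reproduced. The printed denominator is a separate matter, and this point does not depend on it.
- Common SD: √[(25.88² + 21.99²) / 2] = 24.0.

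The documents give no rate for medicine changes, hospital stays or infections. Everything below is illustration under stated assumptions.

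**3. First illustration: events add to the change score.** Let a share p of an arm have an event, let each event add D units to the calprotectin change, and let events be otherwise unrelated to the change.

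- All randomised: difference = (direct effect) + (p_diet − p_control) × D.
- After exclusion: difference = (direct effect) only.
- Amount hidden: (p_diet − p_control) × D.

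With D assumed to be 50 to 100 and no direct effect:

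| Events, control vs diet | Hidden difference | Share of 22.6 |
|---|---|---|
| 10% vs 5% | 0.05 × 50 to 100 = 2.5 to 5 | 11% to 22% |
| 20% vs 10% | 0.10 × 50 to 100 = 5 to 10 | 22% to 44% |
| 30% vs 10% | 0.20 × 50 to 100 = 10 to 20 | 44% to 88% |

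If the rates are swapped between the arms, the same amounts of harm are hidden.

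**4. Second illustration: exclusion follows worsening.** Assume a true difference of 22.6 in favour of the diet and SD 24.0 in each arm. A patient is excluded when a latent worsening score passes a common threshold, set so that 10% to 30% of controls are excluded. The score has the correlation shown with the calprotectin change.

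| Correlation | Diet arm excluded | Expected difference among those left |
|---|---|---|
| 0 | 10% to 30% | about 22.6 |
| 0.3 | 5.9% to 21.0% | 22.1 to 21.7 |
| 0.6 | 3.3% to 13.7% | 20.9 to 19.2 |
| 1.0 | 1.3% to 7.1% | 18.8 to 14.2 |

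Under this mechanism the estimate is undisturbed only when exclusion is unrelated to the outcome. Moderate correlations cost up to about 3.4 units (22.6 − 19.2). The extreme case costs 8.4 (22.6 − 14.2).

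**The case against.** The strongest reply is that the word *excluded* is not defined. The sentence stands under Participants, not under Statistical analysis, and might mean removal from the diet only. An unseen full protocol or SAP might keep these patients in the analysis. This stands as a caution: removal from follow-up and comparison is the natural reading, but it is an inference. It does not dispose of the point, because the article states the rule and nothing in it offsets the rule. If another document says otherwise, the two must be reconciled.

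A second reply is that the rule serves a purpose. Changed medicines, or treatment of an infection, can shift calprotectin and the microbiota in their own right. The effect of the diet under stable medication is a fair question. Dropping the patients answers it without bias only if the events are unrelated to arm and outcome, and the article's own account of calprotectin tells against that.

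Third, event rates may be low. Entrants are described as in remission on stable therapy, with no medicine change in the past month and no hospital stay in three months. A rate of 30% in four weeks is three times the only loss figure the plan gives. This stands. The 10% versus 5% row is the milder scenario, and the last row of the first table should be read as an extreme.

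A reader might infer more than the documents support:

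- *That all disease worsening leaves the comparison.* It does not. Worsening without one of the three events stays in, and some of the events are not worsening of colitis.
- *That exclusion drives the estimate to zero.* In the first illustration it does so by construction, because the diet was assumed to act through events alone.
- *That the matched design collapses.* The article describes the pairs thus: "Therefore, we would have 15 strata (each consisting of two similar persons) in total". An exclusion does leave a pair incomplete, but the planned independent-sample t test does not drop the remaining partner.
- *That lost power is the issue.* Fewer patients do mean less power (70% at 15 per arm, 60% at 12, for a difference of 22.6 by noncentral t). The plan already allows for some loss, and power is a side matter to the bias.

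**Conclusion.** The point holds in limited form. As written, the rule takes out randomised patients for reasons that arise after allocation, that the diet may influence, and that are related to the primary outcome. It can therefore remove part of any disease worsening, perhaps more in one arm than in the other, and bias the primary comparison.

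The documents determine neither the amount nor the direction. Under the assumptions shown, the amount runs from nothing, when exclusion is unrelated to arm and outcome, through 2.5 to 5 units in a mild scenario, to 10 to 20 in an extreme one, against the planned 22.6. The conclusion rests on reading *excluded* as removal from follow-up and analysis. It does not rest on any particular event rate, nor on the sample size calculation.

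**What to change.** For the analysis, replace the exclusion sentence with wording to this effect:

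- All randomised patients are analysed in their allocated group. Every week-4 stool and blood sample available is used, whatever happened to medication, and missing samples are handled by a stated method and reported by arm.
- Medicine change, hospital stay and infection during the intervention are reported by arm.
- The analysis without these patients is kept as a sensitivity analysis.
- The primary analysis is stated to estimate the effect of assignment to the diet regardless of medication changes.

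The cost is mostly wording, with one real downside. The primary estimate will include the effect of any medication changes, which may differ by arm and shift the result systematically, so it is more than added noise. That is why the last statement is needed.

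There is also a practical limit. Trial status reports that recruitment was completed on 30 May 2019. With a two-week run-in and a four-week diet, the last visits would fall around mid-July 2019, before the article appeared in February 2020. Week-4 samples that were not taken may be beyond recovery, but the analysis set and the reporting of events by arm can still be put right. The change concerns who is analysed, not how patients are treated.

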**Fig. 1 Fig1:**
[figure not shown]
Flow diagram of study selection. BMI, body mass index

**Fig. 2 Fig2:**
[figure not shown]
Flow diagram of the study process

### Study design

The study was designed according to the Standard Protocol Items: Recommendations for Interventional Trials (SPIRIT) 2013 checklist. After recruitment, participants will enter into a 2-week run-in period, during which general information on diet, physical activity, type and dosage of medications will be obtained. All measurements, including anthropometric and biochemical assessments, will be made at this stage, and then participants will be stratified based on age (20–40 and 40–60 years), gender (male/female), body mass index (18.5–24.9 and 25–30), and type of medicines (anti-inflammatory and immunosuppressant) into different strata. Actually, first we will enroll a participant who meets the inclusion criteria in a stratum. Then, based on these variables the second person, who is matched with the first one in that stratum would be gone to the same stratum. So, we would have two similar persons (in terms of the aforementioned variables) in a stratum. Then, the two persons in a single stratum would be randomly assigned into the intervention and non-intervention groups. Therefore, we would have 15 strata (each consisting of two similar persons) in total and then individuals in the strata would be randomly allocated to the aforementioned groups. So, we would have 15 people in each group and the groups would be almost similar in terms of these variables. A person who is not part of the study will randomly allocate participants. Participants in the intervention group will receive a low-FODMAP diet according to their usual dietary intakes, whereas participants in the control group will receive their usual diet without any modification, for 4 weeks. Participants in both groups will receive the usual dietary recommendations for patients with IBD. To evaluate participants’ compliance, three 24-h dietary recalls will be taken throughout the intervention. Participants will be asked not to change their life-style and medicines during the study. Again, all measurements will be examined at the end of trial.

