## Trial status

Ongoing, protocol version: 1; 2019-03-19: recruitment began on 1 February 2019 and was completed on 30 May 2019.

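### Baseline samples are taken in the run-in, before pairing, so for the first member of each pair the baseline-to-4-week change also covers the wait for a partner

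*Protocol article*

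**What the plan says.** The Study design section of the protocol article gives a fixed order of events.

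1. After recruitment, "participants will enter into a 2-week run-in period".
2. The baseline is taken in that period: "All measurements, including anthropometric and biochemical assessments, will be made at this stage, and then participants will be stratified based on age".
3. The strata are built from age in two bands and from "gender (male/female), body mass index (18.5–24.9 and 25–30), and type of medicines (anti-inflammatory and immunosuppressant) into different strata".
4. Pairs form one patient at a time. A first eligible patient is placed, and "the second person, who is matched with the first one in that stratum would be gone to the same stratum".
5. Only then is anyone allocated: "Then, the two persons in a single stratum would be randomly assigned into the intervention and non-intervention groups".
6. The target is stated as: "Therefore, we would have 15 strata (each consisting of two similar persons) in total".
7. The diet or usual-diet period of 4 weeks follows, and everything is measured again at its end.

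The Primary outcomes and Secondary outcomes sections provide for two stool samples and two blood samples per patient, one at baseline and one at the end. The primary outcome is the "mean difference in changes from baseline to 4-week follow up in calprotectin concentrations and quantity of gut microbiota between the intervention and control groups". Trial status reports that "recruitment began on 1 February 2019 and was completed on 30 May 2019".

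**The concern.** The first member of a pair cannot be allocated, or start the diet, until a match has been found and has finished its own run-in. By then the first member's calprotectin, lactoferrin, bacterial counts and cytokines have already been sampled, and the article mentions no second sample. Followed literally, the two members of a pair have changes measured over different lengths of time, while the outcome definition treats both as 4-week changes.

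Three things are at stake.

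- **Precision.** An older baseline correlates less well with the end value and lets pre-diet fluctuation into the change score. With 15 patients per group there is little precision to spare.
- **Chance imbalance.** With only 15 pairs, the waiting members' intervals can fall unevenly between the arms.
- **Currency of eligibility.** The Participants section looks back one month for medicine changes and three months for hospitalisation. Its later exclusions apply during the intervention. A wait for a partner falls between these two periods.

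**Working it through.** The protocol gives no figure for the interval between baseline sample and diet start, so there is none to reproduce. The stated sample size does not depend on it.

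**Inputs from the protocol**
- Run-in: 2 weeks. Diet period: 4 weeks (28 days).
- Pairs: 15, so 30 patients (Study design).
- Matching cells: four two-level factors, 2 × 2 × 2 × 2 = 16.
- Recruitment window: 1 February to 30 May 2019 = 118 days (Trial status).

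**Inputs not in the protocol, so assumed**
- How patients arrive, and how common each cell is.
- The correlation between baseline and follow-up.

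**Step 1: the interval implied by the written order**
- Second member: run-in sample to end = 28 days, plus whatever part of the 2-week run-in follows the sample.
- First member: the same, plus the wait W for the partner.
- The interval always contains the full 28 diet days. W cannot exceed the 118-day window.

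**Step 2: the size of W under two arrival processes**

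*Partner sought actively and recruited next.* Thirty patients evenly spaced over 118 days gives W ≈ 118/29 ≈ 4 days.

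*Passive arrivals.* Simulation with patients evenly spaced over 118 days and falling at random into the 16 cells, stopping when 15 pairs are complete:

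| Cell shares assumed | Mean W (days) | Median W (days) | First members with W > 28 days | Longest W per trial, average (days) | Patients enrolled, average |
|---|---|---|---|---|---|
| All factors 50/50 | about 30 | 24 | 42% | 80 | 37 |
| 70/30, 50/50, 60/40, 75/25 | about 25 | 19 | 33% | 74 | 37 |

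With still more uneven shares (70/30, 50/50, 70/30, 90/10) the mean falls to about 20 days.

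At W of 25 to 30 days, a first member's interval is 28 + 25 = 53 to 28 + 30 = 58 days, about double the nominal 28. At W = 4 it is 32 days.

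**Step 3: imbalance between arms**

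Each first member goes to either arm with probability ½, so the expected difference in mean interval is zero. In the two tabulated scenarios the arms' mean intervals differ by about 7 to 8 days on average, and by about 17 to 19 days or more in one trial in twenty. With W = 4 days throughout, the standard deviation of that difference is 4/√15 ≈ 1 day.

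**Step 4: effect on the SD of change (illustration)**

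With equal variance σ² at both times, Var(change) = 2σ²(1 − ρ).
- ρ = 0.6: 2 × 0.4 = 0.8σ².
- ρ = 0.4: 2 × 0.6 = 1.2σ².
- Only first members wait, and they are half of the sample, so the average variance is (0.8 + 1.2)/2 = 1.0σ².
- Ratio of SDs: √(1.0/0.8) = √1.25 = 1.12, a rise of about 12%.

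Both correlations are assumed; the protocol gives neither.

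**The case against.** The strongest reply is that the wait is inferred. No section describes patients waiting. Age, BMI and current medicines are checked for eligibility and sex is evident, so the stratum could be known at enrolment and two run-ins aligned. The outcome sections do not date the baseline sample. The study-process diagram and the additional file are not available here, and a dated visit schedule often sits in the full protocol. This stands as a reason for modest confidence about what happened in practice. It does not remove the order that Study design states: measure first, then stratify, pair and randomise.

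The longer waits also rest on a model that fits the text imperfectly. Passive arrival needs about 37 enrolled patients to complete 15 pairs and leaves about 7 measured but unpaired, whereas the article describes 30 patients and no remainder. Actively seeking each partner fits the wording too and gives about 4 days. This objection stands, so the size has to be given as a range.

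The reply that patients are asked not to change lifestyle or medicines during the study has some force. It lessens the worry about outdated eligibility, but it is not a re-check.

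A reader might also infer four stronger things that the protocol does not support:
- **That the wait is open-ended.** No limit is stated, but the recruitment dates cap it at 118 days.
- **That the change no longer measures the 4-week diet.** The interval is lengthened but still contains all 4 weeks.
- **That the comparison is biased.** Allocation within the pair makes the waiting member equally likely to enter either arm.
- **That the SD of change rises by 22%.** That is √(0.6/0.4), which applies the lower correlation to everyone although only half of the patients wait.

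**Conclusion.** The point holds as a modest, inexpensive improvement. As written, the baseline precedes pairing, nothing limits the wait and nothing renews the sample, so half of the patients have a change score that covers the wait plus 4 weeks. The mean wait lies between about 4 days and about 30 days, depending on an arrival process that the protocol does not state. The upper part of that range (25 to 30 days) assumes passive, even arrivals over 118 days and roughly balanced matching factors. The consequence is added noise and possible chance imbalance in intervals, without systematic bias in the between-group difference. The 12% rise in the SD of change only illustrates the scale and depends entirely on the assumed correlations.

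**What to change.** State in Study design when the outcome baseline is taken relative to randomisation and diet start. Specifically:

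- Keep the run-in for recording diet, activity and medicines.
- Take the single outcome baseline (stool, fasting blood, weight, partial Mayo score and questionnaires) once the pair is complete, within a short pre-specified window before allocation is revealed and the diet starts.
- Re-confirm the existing eligibility criteria at that visit.
- Time the end sample from the first day of the diet period.

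This moves a sample and adds no assays. The cost is a change of wording and tighter scheduling, because both members of a pair must attend within the window.

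Recruitment closed on 30 May 2019, so for patients already sampled the remedy is in reporting. List each patient's interval from baseline sample to start of the diet period, summarise it by arm, and add a sensitivity analysis on it, for example with the interval as a covariate or excluding patients with long intervals. This needs only dates that should already be on record.
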